## Abstract

**Background:**

Workplace violence against health care professionals has increased worldwide, leading to negative psychological, professional, and organizational outcomes. Despite existing prevention and reporting programs, underreporting and lack of accessible, confidential support persist. Digital health tools, including chatbots, may offer scalable support, guidance, and follow-up for affected professionals.

**Objective:**

This study aims to design, develop, and validate a chatbot (*Sanidad Segura*) to assist health care professionals who experience workplace aggression and evaluate its usability, readability, and exploratory indicators of perceived usefulness and support in a pilot study.

**Methods:**

This study will follow a mixed methods design conducted in two main phases: (1) design, development, and content validation of the chatbot based on literature review, institutional protocols, and expert consensus; and (2) pilot-testing, including usability and readability assessment using standardized instruments, as well as feasibility and acceptability evaluation among health care professionals working in emergency and critical care settings in Almería (Spain). The study is aligned with the Medical Research Council framework for complex interventions, incorporating development and feasibility stages. Quantitative data will be collected using the System Usability Scale and Inflesz readability scale. Qualitative data will be collected through semistructured interviews and analyzed using thematic analysis to explore user experience and identify barriers to and facilitators of use.

**Results:**

The study has been funded for a 2-year period starting on December 18, 2024. Quantitative outcomes will include usability scores (System Usability Scale), readability scores (Inflesz), and participants’ sociodemographic characteristics. Qualitative findings will identify themes related to usability, user experience, and suggestions for improvement. Integration of quantitative and qualitative findings will be conducted through triangulation to provide a comprehensive understanding of the usability, acceptability, and readability of the chatbot.

**Conclusions:**

This study addresses the increasing incidence of workplace violence against health care professionals through the development of a new chatbot (*Sanidad Segura*). This intervention seeks to facilitate the identification, support, and follow-up of affected individuals while minimizing the adverse effects of such events on their physical and psychological well-being, social interaction, and professional performance. *Sanidad Segura* will enable confidential case reporting and provide access to tailored medical, psychological, and legal resources, as well as information about institutional support services. This project represents a crucial step toward implementing an integrated digital framework for the detection, management, and prevention of workplace violence in health care settings.

**International Registered Report Identifier (IRRID):**

PRR1-10.2196/92511

## Introduction

Workplace violence constitutes a global public health problem particularly prevalent in settings characterized by high levels of interpersonal interaction, with the health care sector being the most affected [1,2]. In this context, the situation is especially concerning due to the sustained increase in violent incidents over the past decade, with an even more pronounced rise during the recent COVID-19 pandemic [3,4].

The consequences of workplace violence extend beyond the individual, affecting health care workers’ well-being, patient safety, and team dynamics, ultimately reducing the quality of services provided by health care systems [5,6]. Among health care professionals, exposure to workplace violence has been associated with higher levels of burnout, stress, and psychological trauma, as well as decreased job satisfaction [7-9], which, in turn, translates into a greater intention to leave the job [9]. Moreover, workplace violence generates significant costs for health care systems by increasing absenteeism, staff turnover, and the need for replacement personnel, thereby negatively impacting productivity and the economic resources of health care institutions [10,11].

Violence in health care settings may be physical, verbal, or psychological, with the latter being the most frequent and least visible forms [12,13]. Despite their high prevalence, a large number of workplace violence incidents are not formally reported or recorded in official reporting systems, limiting accurate knowledge of their true magnitude and hindering the implementation of preventive and supportive measures [6,14,15].

The problem is particularly acute in emergency departments, which are consistently identified as high-risk settings for workplace violence. Previous studies have reported high rates of verbal and physical aggression among emergency health care professionals, with verbal aggression being the most prevalent form and frequently underreported [16,17]. Global evidence also indicates a higher prevalence of workplace violence in emergency and psychiatric settings than in other hospital services [13,18,19].

In Spain, workplace violence against health care professionals represents a well-documented and growing public health concern. Studies conducted in hospital settings report a high prevalence of aggression, particularly affecting nursing staff and frontline professionals, with nonphysical forms such as verbal and psychological abuse being the most frequent [20,21]. This problem is especially evident in high-demand areas such as emergency departments, where exposure to aggression is common, often involves patients and relatives, and remains substantially underreported [9,13,20].

Within the Andalusian Health Service (*Servicio Andaluz de Salud*), specific protocols for the prevention of and response to aggression against health care professionals have been developed [22]. These institutional measures are currently implemented in the study setting, namely, the Almería Health District, where health care professionals working in emergency and critical care units have access to formal reporting systems, legal support, and preventive protocols. However, aggressive incidents continue to occur, and their psychological impact is not always addressed in an early and systematic manner. This situation highlights the need for complementary tools that facilitate immediate and confidential access to guidance, psychological support, and self-care strategies, contributing to a comprehensive approach to workplace violence in health care settings and reinforcing the effectiveness of existing protocols [13,23].

In this context, the development of innovative digital solutions aimed at supporting health care professionals who have experienced workplace aggression emerges as a promising strategy. Conversational agents based on structured and rule-based architectures have demonstrated utility in health care by providing information, guidance, and emotional support in an accessible and continuous manner [24-26]. There is recent evidence suggesting that this type of technological assistance can be effectively integrated into workplace violence prevention programs, enhancing their reach and effectiveness [26].

However, currently available tools are not usually specifically designed to address workplace violence in health care settings from a comprehensive, professional-centered perspective. Within this framework, *Sanidad Segura* has been developed as a pioneering technological tool aimed at bridging this gap by integrating assistance, emotional support, and referral to legal and psychological resources, offering accessible, safe, and complementary support to existing institutional measures against violence toward health care professionals.

The development of *Sanidad Segura* is guided by the updated Medical Research Council framework for complex interventions. A preliminary program theory underpins the intervention, whereby chatbot components (emotional support, legal guidance, incident reporting, and psychoeducational content) are expected to improve perceived support, reduce barriers to reporting, and enhance help-seeking behaviors. *Sanidad Segura* is designed as a postincident support tool intended to be used after exposure to workplace aggression rather than during acute violent situations. The chatbot provides structured guidance on emotional coping strategies, incident documentation, legal rights, and access to institutional and psychological support services.

The platform operates through a structured conversational workflow based on predefined modules. After accessing the chatbot, users are guided through a sequence of options tailored to their needs following a workplace aggression incident. These modules include (1) emotional support and validation, (2) guidance on how to document and report the incident, (3) information on legal rights and institutional procedures, and (4) access to psychological and occupational support resources. Users interact with the chatbot by selecting options or entering short text inputs, which are categorized using predefined intents and routed through decision tree pathways. The chatbot does not generate free-text responses autonomously; instead, it delivers standardized, expert-validated content adapted to user input.

This study aims to design, develop, and validate this chatbot (*Sanidad Segura*) to assist health care professionals who experience workplace aggression and evaluate its usability, readability, and exploratory indicators of perceived usefulness and support in a pilot study.

## Methods

### Study Design

This study follows a two-phase mixed methods design: (1) design, development, and content validation; and (2) pilot feasibility, usability, and acceptability study. These phases correspond to the development and feasibility stages described in the Medical Research Council framework for complex interventions.

### Study Setting and Participants

Participants will be recruited from health care professionals currently active in emergency and critical care units in the Almería Health District (Spain). Eligibility will be restricted to individuals engaged in active clinical practice within the designated units. Professionals currently enrolled in any formal structured intervention targeting workplace aggression—whether psychological, legal, or organizational in nature—will be excluded. This criterion is intended to prevent potential confounding between ongoing therapeutic or remedial processes and the experimental chatbot exposure, thereby preserving the internal validity of the usability and acceptability assessments.

Sample size estimation for this pilot study was primarily guided by the requirements of the planned summative usability evaluation rather than by hypothesis testing for clinical efficacy outcomes—an approach consistent with current methodological guidance for pilot and feasibility studies of digital health technologies [27,28]. For summative usability assessments using standardized instruments such as the System Usability Scale (SUS), Sauro and Lewis [29] recommend samples of between 40 and 100 participants to achieve margin-of-error estimates of –5 to 10 points to +5 to 10 points at the 95% confidence level, thereby enabling clinically interpretable and psychometrically reliable scoring. Sample sizes within this range also provide sufficient statistical power to detect moderate between-group differences in SUS scores (ie, ≥5 points assuming an SD of approximately 15) and to generate stable estimates of acceptability and perceived usefulness across professional subgroups [29,30]. For pilot feasibility studies specifically targeting digital health interventions, precedent in the published literature supports the use of samples of 40 to 70 participants to ensure adequate precision in the estimation of key design parameters for future confirmatory trials [27,31,32].

Applying these methodological frameworks to the specific population under study and using a finite population correction formula with a 95% confidence level and –5% to +5% precision margin, a minimum of 178 participants is required from an eligible population of 330 professionals. This calculation ensures both representative coverage of the target population and sufficient variability in usability and acceptability responses across clinical roles (physicians, registered nurses, and nursing assistants). Accounting for an anticipated 20% attrition rate, 223 participants will be invited to take part. This sample size substantially exceeds the minimum thresholds recommended for summative usability evaluation and pilot feasibility studies [27,29,31] and, therefore, is considered appropriate to achieve the dual objectives of this study: generating robust usability and acceptability data and informing the design of a subsequent full-scale evaluation.

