### Statistical Analysis

Quantitative data will be analyzed using SPSS (version 30; IBM Corp). A descriptive analysis will be performed for all variables. Continuous variables will be summarized using means and SDs (or medians and IQRs where appropriate), whereas categorical variables will be presented as frequencies and percentages. Normality will be assessed using the Kolmogorov-Smirnov test. Depending on data distribution, parametric tests (Student *t* test and one-way ANOVA) or nonparametric equivalents (Mann-Whitney *U* test and Kruskal-Wallis test) will be applied to compare groups. Associations between categorical variables will be examined using the chi-square test. A significance level of a *P* value of less than .05 will be adopted.

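### The quoted SUS margins of ±5 to ±10 points do not follow from the stated SD of 15, and at that SD power for a 5-point difference is only about 18% to 38%

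*Protocol article*

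**What the plan says.** Under Study Setting and Participants, the protocol article says that the size of the pilot was guided mainly by the summative usability evaluation. It then makes two statements about samples of 40 to 100.

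- **Precision.** It cites a usability reference that is said to "recommend samples of between 40 and 100 participants to achieve margin-of-error estimates"; the range itself is given as "margin-of-error estimates of –5 to 10 points to +5 to 10 points at the 95% confidence level". It gives no SD with this range and does not say whether the margin is for the overall mean, a role subgroup or a difference.
- **Power.** It continues: "Sample sizes within this range also provide sufficient statistical power to detect moderate between-group differences in SUS scores", specified as "ie, ≥5 points assuming an SD of approximately 15". This is the only SD in the document, and no power figure is given.

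The adopted size comes from another calculation, "using a finite population correction formula with a 95% confidence level and –5% to +5% precision margin", which gives 178 of 330 eligible professionals and 223 invited after 20% attrition. Statistical Analysis plans t tests, ANOVA or nonparametric equivalents to compare groups, and says: "A significance level of a *P* value of less than .05 will be adopted". Results reports a convenience sample of 105 and says that group comparisons have been done.

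**The concern.** The two statements stand side by side, concern the same samples and support the same rationale, so a reader will take the SD of the second to apply to the first. It does not reproduce the first, and it does not support the second either.

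Two things are at stake. The first is the precision of the main usability result. The SUS bands between 60 and 89 in Usability Assessment are 10 points wide. An interval of ±10 covers two band widths, whereas ±2.9 covers 5.8 points and can lie within one band. The second is how group comparisons are read. If readers believe that samples of this size can detect 5 points, they may take a nonsignificant comparison between roles as evidence of similar usability.

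The obtained sample makes this more important. With 105 participants the 178 was not reached, so the usability and pilot ranges in this paragraph are the stated size criteria that the sample still meets.

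**Working it through.** **Inputs.** From Study Setting and Participants: n = 40 to 100, margin ±5 to ±10 at 95% confidence, difference 5 points, SD about 15, population 330, attrition 20%. From Statistical Analysis: alpha 0.05. From Results: n = 105. Assumptions made here: two-sided tests, two equal groups, and a proportion of 0.5 in the finite-population formula.

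**1. The adopted size.** n0 = 1.96² × 0.25 / 0.05² = 384.15. With the correction, 384.15 / (1 + 383.15/330) = 177.8, which rounds up to 178. Then 178 / 0.8 = 222.5, which rounds up to 223. Both figures reproduce, and neither uses the SUS margin or the SD.

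**2. Margin of the overall mean at SD 15.** Margin = t(0.975, n−1) × 15 / √n.

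| n | 95% margin |
|---|---|
| 40 | ±4.80 |
| 70 | ±3.58 |
| 100 | ±2.98 |
| 105 | ±2.90 |

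No size in the range gives a margin as wide as ±5. A finite-population correction only tightens the figures (±4.5 at 40, ±2.5 at 100). Conversely, at SD 15 a margin of ±5 needs 38 participants and ±10 needs 12. The stated range is therefore not reproduced for the overall mean.

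**3. Other quantities the margin could describe, at SD 15.**

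- One of three equal role groups: ±9.1 (total 40) to ±5.3 (total 100).
- Difference between two equal halves: ±9.6 (total 40) to ±6.0 (total 100).

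Both lie within ±5 to ±10.

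**4. Power for 5 points at SD 15.** For two groups of n/2, SE = 15 × √(4/n). At a total of 100, SE = 3.0 and 5/3.0 = 1.667, so the normal approximation gives Φ(1.667 − 1.96) ≈ 38%. Results from the noncentral t and the normal approximation:

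| Total | Noncentral t | Normal |
|---|---|---|
| 40 | 17.7% | 18.3% |
| 70 | 28.0% | 28.6% |
| 100 | 37.9% | 38.5% |
| 105 | 39.4% | 40.0% |
| 178 | 59.9% | 60.4% |

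If 40 to 100 is read as the size of each group, power is 32% to 65% (normal). One-sided testing, which the plan does not mention, would give 28% to 51% at totals of 40 to 100. For 80% power, 2 × (1.96 + 0.842)² × (15/5)² = 141.3, so 142 per group or 284 in total.

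**5. Do the two sentences fit together under any SD?** If the overall mean has margin M, the difference between two equal halves has a margin of about 2M. At M = 5 that is ±10, an SE of about 10/1.96 = 5.1, and power for 5 points of about 17%. If instead the margin is for a third of the sample or for a difference, so that SD 15 fits, power at totals of 40 to 100 is still the 18% to 38% of step 4.

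**The case against.** The strongest reply is that the margin range is a rule of thumb from a cited source, given without an SD, and that it serves only as a floor which the adopted 178 clears. At SD 15 every size from 40 to 100 achieves ±5 or better, so the sentence is true as an upper bound. The pairing of ±5 with n=40 alone implies an SD of 5 × √40 / 2.02 ≈ 15.6, close to 15. The whole range also fits SD 15 if it refers to role subgroups or to a difference. If the range is loose, it errs on the cautious side.

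Much of this stands. A reader might infer that the plan rests on two incompatible SDs, because an exact match for the overall mean would need about 31 for ±10 at n=40 and about 25 for ±5 at n=100. The document states one SD only. The larger values are back-calculated and assume both an exact half-width and the overall mean, so they should not be attributed to the authors. Nor should one say that the margin is more than three times too wide at n=100: that pairs ±10 with n=100, which the document never does and which would need an SD of about 50. The mismatch does not make the 178 or the 223 wrong either.

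What does not stand is the power sentence. It uses the document's own difference and SD, and no reading of 40 to 100 brings power above 65%.

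**Conclusion.** The point holds in limited form. Read as the margin of the overall mean, ±5 to ±10 is wider than the stated SD gives (±4.8 to ±3.0) and is met only as a loose upper bound. Because the quantity is not named, this part is unclear wording more than proven error.

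The power statement is the substantive fault. At SD 15, power for 5 points is about 18% to 38% for totals of 40 to 100, and about 39% for the 105 obtained. This assumes two equal groups and a two-sided 5% test; unequal groups or a split into three roles would lower it.

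Nothing in the design calculation changes. The correction concerns how the precision and the group comparisons of the obtained sample are presented.

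**What to change.** 1. State what the margin refers to (overall mean, role subgroup or difference) and use SD 15 throughout the paragraph. If it is the overall mean, replace ±5 to ±10 with ±4.8 (n=40) to ±3.0 (n=100).
2. Give the margin for the 105 obtained, about ±2.9 at SD 15, and update it with the observed SD.
3. Replace the power claim with the actual 18% to 38%, or delete it and label the between-group SUS comparisons exploratory. Correcting the margins alone is not enough, because the power claim would remain.
4. Do not bring in an SD of 25 to 31 to rescue the quoted range, since nothing in the document supports it.

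The cost is rewording two sentences and adding one figure from data already collected.

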## Results

The study has been funded for a 2-year period starting on December 18, 2024. This study will generate both quantitative and qualitative outcomes to evaluate the chatbot. Quantitative outcomes will include usability scores measured using the SUS and readability scores assessed using the Inflesz scale, along with participants’ sociodemographic characteristics.

Data collection was conducted between February and May 2026. A final convenience sample of 105 participants was obtained. At the time of manuscript submission, data analysis had been completed using SPSS Statistics (version 30.0; IBM Corp). The analyses included descriptive statistics, group comparisons, and correlation analyses as part of the pilot study. The results are expected to be published in an open-access journal in September 2026, with a potential second publication derived from the qualitative analysis anticipated in 2027. Qualitative findings will be derived from semistructured interviews, allowing for an in-depth exploration of user experience. Thematic analysis will be used to identify key themes related to usability, user experience, and suggestions for improvement.

Finally, quantitative and qualitative findings will be integrated through a convergent mixed methods approach using triangulation techniques to provide a comprehensive understanding of the usability, acceptability, and readability of the chatbot.

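### Samples of 40 to 100 do not give sufficient power for a 5-point SUS difference at SD 15: power is about 18% to 38%, and 39% at the achieved 105

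*Protocol article*

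**What the plan says.** All of the following is in the protocol article.

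- **Study Setting and Participants, sample size paragraph.** For summative usability work, the authors cite a source said to "recommend samples of between 40 and 100 participants". They go on to say that sample sizes in this range also "provide sufficient statistical power to detect moderate between-group differences in SUS scores (ie, ≥5 points assuming an SD of approximately 15"). No power percentage, sidedness or group ratio is given.
- **Study Setting and Participants, next paragraph.** The planned minimum of 178 out of 330 eligible professionals, with 223 invited, comes from a finite-population precision formula. The three clinical roles named are physicians, registered nurses and nursing assistants.
- **Statistical Analysis.** The t test, one-way ANOVA or their nonparametric equivalents "will be applied to compare groups", and a P value "of less than .05 will be adopted" as the significance level.
- **Results.** "A final convenience sample of 105 participants was obtained". The completed analyses are said to include group comparisons.

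**The concern.** The power sentence supplies a difference, an SD and a sample size range, so it can be checked. A 5-point difference at SD 15 is a standardized difference of one third, and detecting that between two independent groups normally takes well over 100 people per group, not 40 to 100 altogether.

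The sentence bears on how the results will be read. The achieved 105 lies just above the range described as adequately powered, so a reader would apply the assurance directly to the reported comparisons. A non-significant comparison between, say, nurses and physicians would then look like evidence that the chatbot is about equally usable for both. If power is really below 40%, a true 5-point gap would be missed more often than found. The protocol also wants this pilot to inform a full-scale evaluation, and the same planning assumption carried forward could make that study too small.

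**Working it through.** **Inputs**

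- Difference 5 points, SD 15, so d = 5/15 = 0.333 (Study Setting and Participants).
- Total N of 40 to 100 (same section); also the achieved 105 (Results), the planned 178, and the 223 invited.
- Alpha 0.05 (Statistical Analysis).
- Assumed, because not stated: two-sided test, two equal groups (the most favourable split), N as a total, and 80% as the usual minimum for sufficient power.

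**The plan's own sample size.** With p = 0.5, 95% confidence and a ±5% margin, n0 = 1.96² × 0.25 / 0.05² = 384.16. The finite-population correction gives 384.16 / (1 + 383.16/330) = 177.8, so 178. Then 178 / 0.8 = 222.5, so 223. Both stated figures reproduce, and neither uses the power sentence. The plan gives no power percentage to reproduce, only the word sufficient.

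**Power for 5 points.** The standard error of the difference with N/2 per group is 15 × √(4/N). Approximate power is Φ(5/SE − 1.96). The exact figures use the noncentral t distribution. The last column is the difference detectable with 80% power (noncentral t).

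| Total N | SE | 5/SE | Power, normal | Power, noncentral t | Detectable at 80% |
|---|---|---|---|---|---|
| 40 | 4.74 | 1.05 | 18.3% | 17.7% | 13.6 points |
| 70 | 3.59 | 1.39 | 28.6% | 28.0% | 10.2 points |
| 100 | 3.00 | 1.67 | 38.5% | 37.9% | 8.5 points |
| 105 | 2.93 | 1.71 | 40.1% | 39.4% | 8.3 points |
| 178 | 2.25 | 2.22 | 60.4% | 59.9% | 6.3 points |
| 223 | 2.01 | 2.49 | 70.2% | 69.8% | 5.7 points |

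**Size needed for 80% power.** n per group = 2 × (1.96 + 0.842)² × (15/5)² ≈ 141.3 by the normal approximation, and 142.2 by the noncentral t. That is 143 per group, 286 in total, out of an eligible population of 330.

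**Other readings of the range 40 to 100**

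| Reading | N = 40 | N = 100 |
|---|---|---|
| Total N, one-sided | 27% | 50% |
| N per group, two-sided | 31% | 65% |
| N per group, one-sided | 43% | 76% |
| Total N, 2:1 split, two-sided | 16% | 34% |
| Three-group ANOVA, largest gap 5 points | 11% to 12% | 21% to 26% |

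The ANOVA range runs from means of −2.5, 0, +2.5 to means of 0, 0, 5. At N = 105 a 70/30 split gives 34% power and a detectable difference of 9.0 points; the three-group ANOVA gives 21% to 28%.

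Only a one-sample or paired test at N = 100 passes 80% (91%), and that is not a between-group comparison.

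**The case against.** The strongest reply is that nothing in the design rests on this sentence. The 178 and 223 come from the precision formula, the study is presented as a feasibility and usability study, and data collection and quantitative analysis are finished. That is correct, and it limits the consequence to interpretation. It does not make the sentence true.

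A second reply is that the sentence is loosely worded. It gives no power figure, sidedness or allocation, and the range might mean participants per group. So 18% to 38% is one reading, though the natural one for a sample of 40 to 100 participants. On the per-group reading at 100, a 5-point gap would be found more often than missed. No between-group reading reaches 80%, however. Nor does the wording of at least 5 points help, since it sets 5 as the threshold and the real threshold is 8.5 to 13.6 points.

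Third, if inference is confined to the 330 eligible staff and a finite-population correction is applied, the normal approximation gives about 51% at 100, 54% at 105 and 91% at 178. The planned tests do not mention such a correction, and the range in the sentence still falls short with it. The point does have force against the 60% quoted for 178: that figure depends on the inference frame. The protocol makes no power claim for 178 in any case, so it is given here only for scale.

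Finally, the protocol does not name the groups to be compared, and nowhere says that a non-significant result will be read as equality. That risk is inferred from the assurance the sentence gives, combined with testing at P<.05.

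**Conclusion.** The concern holds. On the protocol's own difference and SD, a total of 40 to 100 participants gives about 18% to 38% power for 5 points, and the achieved 105 gives 39%. These figures assume a two-sided 5% test, two equal groups and no finite-population correction. Unequal groups or a three-role comparison lower them. The most generous between-group alternative examined stops at 76%. The sample that was obtained has 80% power only for differences of about 8.3 points or more.

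The claim is a plain error and needs correcting, but its reach is limited: it affects what can be concluded from the group comparisons, and leaves the stated sample size and the descriptive usability estimates untouched.

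**What to change.** Delete the power sentence in Study Setting and Participants, or replace it with wording such as: *With 105 participants in two equal groups and an assumed SD of 15, a two-sided 5% test has 80% power only for SUS differences of about 8.3 points or more; power for 5 points is 39%. Subgroup comparisons are exploratory, and a non-significant result is not evidence of equal usability.*

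Because 105 is the achieved number, say that the figure was calculated after recruitment from the planning SD, so that it is not mistaken for the original rationale or for power computed from observed results. If the authors prefer to keep achieved numbers out of the planning section, deletion there plus the exploratory label in Statistical Analysis is enough.

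In either case, report each between-group SUS difference with its 95% confidence interval. With equal groups at N = 105 and SD 15, the half-width is about 1.96 × 2.93 = 5.7 points, which shows the reader directly that a 5-point gap cannot be excluded when the observed difference is near zero.

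The cost is a few sentences and a less favourable stated figure. No additional participants or data are needed.

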#### Usability Assessment

Usability will be measured using the SUS [34,35], a validated 10-item questionnaire assessing perceived usability across dimensions such as learnability, efficiency, and satisfaction. Each item is rated on a 5-point Likert scale. Final scores range from 0 to 100, with higher scores indicating better usability. Scores will be interpreted as follows: poor (<60), marginal (60-69), acceptable (70-79), good (80-89), and excellent (≥90).

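### The stated minimum of 178 for ±5% precision is not reconciled with the 105 participants obtained, and the ±5% describes a proportion, not the SUS score

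*Protocol article*

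**What the plan says.** The protocol article's Study Setting and Participants section first says that the sample size was "primarily guided by the requirements of the planned summative usability evaluation rather than by hypothesis testing". It cites guidance on SUS studies whose authors "recommend samples of between 40 and 100 participants to achieve margin-of-error estimates" of 5 to 10 points either way, and it gives a working SD in the remark "≥5 points assuming an SD of approximately 15". It also cites 40 to 70 participants as usual for digital pilot studies.

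The next paragraph derives the size differently, "using a finite population correction formula with a 95% confidence level and –5% to +5% precision margin". The result is that "a minimum of 178 participants is required from an eligible population of 330 professionals". The article says this calculation guarantees that the target population is represented and that responses vary enough across clinical roles. It then adds an allowance: "Accounting for an anticipated 20% attrition rate, 223 participants will be invited to take part".

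Usability Assessment describes the SUS as a score: "Final scores range from 0 to 100, with higher scores indicating better usability". Phase 2: Pilot-Testing describes recruitment of a convenience sample by email invitation. The Results section reports that data collection ran from February to May 2026, that the quantitative analysis is complete, and that "A final convenience sample of 105 participants was obtained".

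**The concern.** The article calls 178 a required minimum and reports 105, with no sentence connecting the two. It was written after recruitment had closed, so the gap was known, yet the precision target and the assurance about representation stand unqualified.

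The ±5% is also not tied to any outcome. The text says the size was guided by the SUS evaluation, then applies a formula for percentages. No proportion is named as its target, and the SUS is a 0 to 100 score. A reader cannot tell what the ±5% refers to, and the article does not give the precision of the mean SUS at the number obtained.

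At stake is what readers of the results, and designers of the full-scale evaluation this pilot is meant to inform, will take from the section: a margin for percentages that was not reached, a claim of representation that a convenience sample cannot support, and an allowance that leaves no separate room for people who do not answer an email.

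**Working it through.** **Inputs from the protocol article.** Eligible population N = 330, 95% confidence (z = 1.96), margin e = 0.05, minimum 178, allowance 20%, invitations 223, SUS SD about 15 (all Study Setting and Participants); achieved n = 105 (Results). **Assumption:** p = 0.5. The article does not state it; it is inferred because it reproduces 178.

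**1. Reproduce the planned size.** For a proportion with finite population correction:

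n = N z² p(1−p) / [e²(N−1) + z² p(1−p)] = 330 × 3.8416 × 0.25 / (0.0025 × 329 + 3.8416 × 0.25) = 316.93 / 1.7829 = 177.8, rounded up to 178.

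With the allowance, 178 / 0.8 = 222.5, rounded up to 223. Both figures reproduce.

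**2. Check whether 178 could belong to the mean SUS.** For ±5 points at SD 15: (1.96 × 15 / 5)² = 34.6, so 35 participants. With the correction, 34.57 / (1 + 33.57/330) = 31.4, so 32. The 178 is therefore not a SUS calculation.

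**3. Shortfall.** 105 / 178 = 59% of the stated minimum.

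**4. Margin for a proportion, same formula.** Margin = z √[p(1−p)/n] × √[(N−n)/(N−1)].

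- n = 178, p = 0.5: 7.35% × √(152/329) = 4.99%, as planned.
- n = 105, p = 0.5: 1.96 × √(0.25/105) = 9.56% uncorrected; × √(225/329) = 7.91% corrected.
- n = 105, other p, corrected: ±7.7 points at p = 0.6, ±7.2 at 0.7, ±6.3 at 0.8, ±4.7 at 0.9.

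The ±7.9 is thus the largest corrected value over p.

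**5. Margin for the overall mean SUS at n = 105.** With t on 104 degrees of freedom:

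- SD 15: 1.983 × 15/√105 = ±2.9 points; × √(225/329) = ±2.4 with correction.
- SD 20 (an assumed, less favourable value): ±3.9 points uncorrected.

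**6. The 20% allowance.** It is applied to people invited. Reaching 178 from 223 requires 178/223 = 80% of those emailed to consent and complete, so the one figure has to cover non-response as well as attrition.

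**The case against.** The strongest reply is that nothing was miscalculated and nothing was hidden. The 178 and 223 are correct, the sizing paragraph is prospective, and the Results section openly prints 105. Missing a recruitment target is a matter of conduct and does not make the plan wrong. The article never attaches ±5% to the 105, and none of its listed quantitative outcomes (SUS, Inflesz, sociodemographic description) is a prespecified proportion. The size was said to be guided mainly by the SUS evaluation, and 105 exceeds both cited ranges, 40 to 100 and 40 to 70.

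Most of this stands. There is no arithmetic error, and the usability outcome is not harmed. It is also fair that ±7.9 depends on an inferred p and on random sampling, so it cannot simply replace ±5% as if it were sound. Deleting the 178 now would be worse than leaving it, since it would hide the original target.

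The reply does not explain why an article written after data collection leaves a required minimum and an assurance of representation unqualified beside a convenience sample of 59% of that size. At 105 the sample is also only just above the upper cited figure of 100, so the remark that the size comfortably exceeds the usability thresholds no longer fits.

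**Conclusion.** The point holds as a reporting inconsistency that should be fixed; it does not threaten the study's main usability result. The stated minimum was not reached (105 against 178) and the article does not reconcile the two. The ±5% belongs to a single proportion at p = 0.5. At 105 that margin is at worst about ±7.9 percentage points with finite population correction and ±9.6 without. These figures assume simple random sampling, which was not used, so they are nominal and do not by themselves support a claim of representation. The precision relevant to usability is about ±2.9 SUS points for the overall mean at SD 15, or ±2.4 with correction.

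A reader might go further in two ways that the article does not support. One is to conclude that the usability estimate is too imprecise; on the article's own SD and cited ranges it is not. The other is to quote a response rate. It would be 105/223 = 47% if 223 were invited and 105/330 = 32% if everyone eligible was, but the number actually invited is not reported, so neither can be asserted.

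**What to change.** - Under Study Setting and Participants, keep 178 as the planned target and add that 105 were obtained. Repeat this in Results, with a sentence acknowledging the shortfall.
- State that the ±5% applied to a proportion, with p = 0.5 if the authors confirm it, and that it was not achieved. Give about ±7.9 percentage points (corrected) and ±9.6 (uncorrected) as worst-case, nominal margins for any percentage reported.
- Give the precision for the usability outcome: mean SUS about ±2.9 points at SD 15, or ±2.4 with correction, to be replaced by the interval from the observed SD when results are published.
- Withdraw, for the achieved convenience sample, the claim that the calculation secures representation of the target population.
- As a minor point, report the number actually invited, and label the 20% as covering non-response as well as attrition.

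The cost is a few sentences and figures already computed above. No new participant data are needed. The authors give up a more favourable margin for percentages and gain a clear statement of the adequate SUS precision.
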